## Abstract

**Background:**

Most antidepressant treatment studies have included patients strictly based on the Diagnostic and Statistical Manual of Mental Disorders definition of Major Depressive Disorder (MDD). Given the heterogeneity of MDD, this approach may have obscured inter-patient differences and hampered the development of novel and targeted treatment strategies. An alternative strategy is ​​to use biomarkers to delineate endophenotypes of depression and test if these can be targeted via mechanism-based interventions. Several lines of evidence suggest that “inflammatory depression” is a clinically meaningful subtype of depression. Preliminary data indicate that omega-3 fatty acids, with their anti-inflammatory and neuroprotective properties, may be efficacious in this subtype of depression, and this study aims to test this hypothesis.

**Method:**

We conduct a match-mismatch-trial to test if add-on omega-3 fatty acid eicosapentaenoic acid (EPA) reduces depressive symptoms in patients with MDD and systemic low-grade inflammation. MDD patients on a stable antidepressant treatment are stratified at baseline on high sensitivity-C-reactive protein (hs-CRP) levels to a high-inflammation group (hs-CRP ≥ 3 mg/L) or a low-inflammation group (hs-CRP < 3 mg/L). Both groups receive add-on EPA (2 g per day) for 8 weeks with three study visits, all including blood draws. Patients and raters are blind to inflammation status. Primary outcome measure is change in Hamilton Depression Rating Scale score between baseline and week 8. We hypothesize that the inflammation group has a superior antidepressant response to EPA compared to the non-inflammation group. Secondary outcomes include a composite score of “inflammatory depressive symptoms”, quality of life, anxiety, anhedonia, sleep disturbances, fatigue, cognitive performance and change in biomarkers relating to inflammation, oxidative stress, metabolomics and cellular aging.

**Discussion:**

In this study we will, for the first time using a match-mismatch trial design, test if omega-3 is an efficacious treatment for inflammatory depression. If our study is successful, it could add to the field of precision psychiatry.

**Trial registration:**

This trial was registered May 8, 2017 on clinicaltrials.gov under the reference number NCT03143075

## Background

Among psychiatric disorders, depression is the number one cause of disability worldwide, and the overall second largest contributor to Years Lived with Disability [1]. Despite this, the pathophysiological mechanisms of depression are not fully understood and there are no clinically established biomarkers guiding treatment selection [2]. The poor remission rates with currently available treatments, most of which act on monoaminergic systems, suggest that there may be additional targets that could be therapeutically engaged [3].

The symptom heterogeneity of Major Depressive Disorder (MDD) may have hampered our understanding of the underlying biological mechanisms and slowed down the development of targeted pharmacological interventions. Therefore, we need biomarkers that could delineate more homogenous subsamples within this inclusive and heterogeneous diagnostic category, in order to test individualized treatments. Precision medicine, taking into account unique features of a patient’s pathology in selecting treatments, and improved patient stratification have been suggested as strategies to address issues of diagnostic heterogeneity [4]. A proposed, and widely studied, pathophysiological mechanism in depression is systemic low-grade inflammation. Available evidence suggests, however, that MDD is not an inflammatory disorder per se, but inflammation may rather contribute to the pathophysiology in some, but not all, cases of depression [5, 6]. The association between inflammation and depression has been studied extensively, and has been reviewed by our research group and others [6, 7]. In most published studies, MDD patients have higher mean levels of peripheral inflammatory markers compared to controls [8, 9], although there is a significant between-group overlap. Also, some patients treated with cytokine interferon-alpha (IFN-α) for hepatitis and other illnesses go on to develop depressive symptoms, further supporting the role of inflammation as a causative factor of depression [10]. Accumulating evidence suggests that some depressive symptoms are more inflammatory than others. Results from several large-scale studies show an association between inflammation and a specific depression symptom profile of anhedonia, lack of energy, sleep and appetite disturbances [11–14]. These symptoms overlap with so-called “sickness behavior”, seen in both humans and animals during states of infection [15].

It is still not clear whether alterations of immune markers seen in some depressed patients are caused by mechanisms in the periphery and/or in the central nervous system [16]. Animal studies have shown that depressive-like behavior may be mitigated by counteracting the effects of pro-inflammatory cytokines either in the blood or the brain [17]. Based on these reports and complementary clinical studies [18], interventions targeting inflammation in the periphery could be efficacious in treating psychiatric symptoms [17].

Several investigators have advocated for stratifying subjects based on inflammation status when designing clinical trials testing the antidepressant effect of anti-inflammatory drugs [17, 19, 20]. High-sensitivity C-Reactive Protein (hs-CRP) has been suggested as a candidate biomarker for this purpose [16, 21]. Hs-CRP can easily be obtained from a simple blood test and there are established cut-offs defining low-grade inflammation [22], as described in more detail below. Plasma hs-CRP may be a useful surrogate marker for both peripheral and central inflammation as it correlates with other inflammatory markers in blood and cerebrospinal fluid [16, 23]. Moreover, mean hs-CRP levels are increased in MDD compared to controls [24] and higher blood hs-CRP has been associated with changes in brain areas involved in motivation and motor activity; two important aspects of depressive symptomatology [25].

### Can omega-3 fatty acids be used to treat “inflammatory depression”?

Supplementation of polyunsaturated fatty acids (PUFAs) to individuals with cardiovascular disease decreases plasma levels of hs-CRP [26]. PUFAs omega-6 (n-6) and omega-3 (n-3) have several immune-modulating effects and are regarded as pro- and anti-inflammatory respectively [27]. They are found in cell membranes and compete for the same enzyme (delta 6-desaturase) for metabolization. Availability of n-6 in the cell membranes leads to the production of arachidonic acid (AA) and downstream pro-inflammatory agents such as prostaglandin E2. On the contrary, availability of n-3 PUFAs leads to more eicosapentaenoic acid (EPA) and docosahexaenoic acid (DHA) which in turn metabolize to anti-inflammatory agents resolvins and protectins [28]. These molecules exert their anti-inflammatory effects via various mechanisms including suppression of AA production. Hence, the balance between n-3 and n-6 PUFAs contribute to downstream formation of pro- or anti-inflammatory agents [7]. Humans have sparse or little de novo production of EPA and DHA [29] and are therefore dependent on dietary consumption of these compounds, which are readily available in fish and therefore called “marine PUFAs”. In addition to these mechanisms, other anti-inflammatory properties have also been attributed to n-3 fatty acids. These include (but are not limited to): 1. Reduced neutrophil and monocyte chemotaxis, 2. Reduction of adhesion molecule expression in the circulation and on immune cell surfaces, e.g. vascular cell adhesion molecules (VCAM) and intercellular adhesive molecules (ICAM), 3. Reduced prostaglandin production and 4. Suppressed proliferation of T-cells [as reviewed in 30]. The underlying mechanisms of these effects are still not completely known, but may involve n-3 fatty acids acting via cell surface and intracellular receptors regulating inflammatory cell signaling and gene expression patterns [30]. Besides anti-inflammatory effects, n-3 fatty acids may also have positive effects on leukocyte telomere length, telomerase activity, and other oxidative stress and cell aging markers [31]. However, more research is needed in order to confirm the effects of n-3 fatty acids on these biological processes and to determine any clinical relevance.

N-3 fatty acids have been found in some, but not all, studies to be superior to placebo in treating unipolar or bipolar depression, and the antidepressant effect of EPA has been greater than DHA [32]. Several reasons for caution have, however, been highlighted when interpreting these results, such as the small and possibly clinically irrelevant effect sizes and publication bias [33]. It is possible, given the anti-inflammatory properties of n-3 fatty acids, that this intervention is more efficacious in a subgroup of depression characterized by systemic low-grade inflammation. Consistent with this hypothesis, one Randomized Controlled Trial (RCT) showed that EPA (but not DHA) was effective in preventing IFN-α induced depression in patients with hepatitis C [34]. Consistent with a therapeutic effect of n-3 fatty acids in inflammatory depression, post hoc analyses from another RCT showed that EPA, but not DHA, was superior to placebo in reducing depressive symptoms but only in those depressed subjects with high inflammation markers at baseline [18]. Interestingly, effect sizes were large in this subgroup of inflammatory depression and increased with the number of inflammatory markers elevated. While these findings are suggestive of a specific effect of EPA on inflammatory depression, studies selecting patients a priori based on inflammatory markers are needed to confirm or refute this hypothesis.

### The main aims of this trial are to test if

Add-on EPA enriched n-3 has an antidepressant effect in patients with pre-treatment hs-CRP elevations.The antidepressant effect is mediated by changes in inflammatory markers during the course of the study.The current trial design with a priori stratification using inflammatory biomarkers is feasible, which could advance “precision psychiatry”.

## Methods

### Study design

This is a match-mismatch study with two parallel groups all receiving the same intervention. Participants are stratified according to inflammation status to a “low inflammation” or “high inflammation” group, based on high-sensitivity CRP (hs-CRP) levels before start of treatment. Participants and raters of the outcome measures are blind to group allocation during the study. Hs-CRP ≥ 3 mg/L is used to define the inflammation group based on recommendations from the Centers for Disease Control and the American Heart Association [22]. This cut-off has also been used in several depression studies to define low-grade inflammation [16, 18, 21]. Subjects will be instructed to postpone blood draw if they experience any signs of infection or sickness, and all study protocol deviations are noted. All subjects receive the same intervention of EPA 2 g/day added to their ongoing, stable medication.

### Primary and secondary outcomes

The primary outcome is absolute change in depressive symptoms between baseline and week 8, as measured with the Hamilton Depression Rating Scale 17-items (HAM-D-17). Secondary outcome measures are: Montgomery-Åsberg Depression Self-Rating Scale [35]; “inflammatory depressive symptoms”, defined as a composite score of Patient Health Questionnaire-9 [36] items #3 (sleep problems), #4 (lack of energy), #5 (appetite disturbance); overall function and quality of life using World Health Organization Disability Assessment Schedule [37]; anxiety symptoms using the Generalized Anxiety Disorder 7-item scale [38]; anhedonia using the Snaith-Hamilton Pleasure scale [39]; sleep disturbances using the Insomnia Severity Index [40]; fatigue using the Fatigue Severity Scale [41]; and speed of information processing, sustained attention and visual working memory using the Digit Symbol Coding Test [42].

### Overview and setting

The study was initiated in 2017 at the psychiatric clinic in Lund, Sweden. The study was approved by the ethical review board in Lund, Sweden (ref #2017/150). Amendments to the study protocol have been made, and approved, to improve recruitment and study procedures. To ensure proper collection and documentation of study results, records of study procedures and compliance with the approved protocol, the study is monitored by Clinical Studies Sweden, Forum South. Subjects are recruited via social media ads or clinical referrals.

At the screening visit, confirmation of MDD diagnosis according to DSM-5 and screening for potential comorbidities is carried out using the Mini International Neuropsychiatric Interview (MINI) [43]. As additional inclusion criteria, we chose cut-offs on the HAM-D-17 and the Clinical Global Impression scale (CGI) [44] in line with the proof-of-concept study from Rapaport et al. reporting that EPA might be efficacious in inflammatory depression [18]. Symptom rating scales and biomarkers are assessed at baseline, at weeks 4 and 8 (end of study).

### Eligibility criteria

Inclusion criteria:Age 18–80 yearsDSM-5 criteria fulfilled for current unipolar depressive episode (duration of symptoms > 4 weeks)HAM-D-17 score ≥ 15CGI severity score ≥ 3Stable antidepressant or mood stabilizing treatment 6 weeks before study startSubjects agree to not significantly modify their diet during the study

Exclusion criteria:Medical illness that is serious or unstable and in the investigator's opinion could jeopardize response to treatment or interpretation of study results (e.g. malignancy, active or in remission < 1 year, insulin-dependent diabetes mellitus, active autoimmune disorder or inflammatory bowel disease)Allergy to the study compoundsCurrent infectionPregnancy or breast-feedingDiagnosed psychotic or bipolar disorder, dementia, mental retardation, or individual who lack the ability to make an informed decision due to other conditionsCurrent electroconvulsive therapyAnticoagulant treatment or known bleeding disorderCurrent, serious suicidal or homicidal risk, in the judgment of investigatorSubstance use disorder, except nicotine or caffeine, in the 3 months preceding the screening visitAny medications that could confound the biomarker analyses, within 1 week of baseline or throughout the trial, including: regular intake of non-steroidal anti-inflammatory drugs (NSAIDs) or cyclooxygenase-2 (COX-2) inhibitors, or any use of oral steroids, immunosuppressants, chemotherapy, interferon. Patients will be instructed against intake of NSAIDs (including Aspirin) or COX-2 inhibitors in the 24 h preceding a visit including biomarker assessment visitIntake of n-3 fatty acid supplementation for 3 consecutive days or more in the month preceding the screening visitInitiation of psychotherapy during the last 4 weeks or plan to start psychotherapy during the studyActive participation with ongoing study visits in other clinical studies

### Study procedures

The study intervention is initiated at the baseline visit and continues for 8 weeks with additional study visits after four weeks and after eight weeks of treatment, as shown in Fig. 1.

**Fig. 1 Fig1:**
[figure not shown]
Schematic flow-chart describing the study protocol. Abbreviations: Hamilton Depression Rating Scale 17-item (HAM-D-17), World Health Organization Disability Assessment Schedule 2.0 (WHODAS 2.0), Mini International Neuropsychiatric Interview (MINI), Generalized Anxiety Disorder 7-item scale (GAD-7), Patient Health Questionnaire-9 (PHQ-9), Montgomery Åsberg Depression Rating Scale (MADRS-S), C-Reactive Protein (CRP), Eicosapentaenoic acid (EPA)

Study eligibility is determined at the screening visit. The study physician conducts a review of systems and a complete medical history. Also, MINI interview, HAM-D-17 rating, and blood draw (hs-CRP) are assessed in order to determine eligibility. At baseline, week 4, and week 8 study visits, a larger blood draw (total of 36 ml each time) is carried out, and symptoms assessed using the rating scales outlined below. The Digit Symbol Coding test is completed at baseline and week 8.

Subjects eligible for inclusion start treatment with 2 g EPA per day*.* Subjects receive detailed instructions for how to take the capsules, and the number of remaining capsules are counted at each study visit to determine patient adherence. Subjects are provided with a “diary” and instructed to note the capsules taken (and any missed doses).

There is currently no consensus on the optimal EPA dose for treating depressive symptoms, with formulations ranging from approximately 1 g/day to 4 g/day [33], although doses as high as 9.6 g/day have been used in studies on depression with few and very mild side effects [45]. A recent meta-analysis on n-3 fatty acid supplementation in major depression showed similar numbers of adverse events in intervention and placebo groups [46]. Adverse events were predominantly gastrointestinal but psychological and other physical adverse events have also been reported [46]. There is a theoretical possibility that n-3 fatty acids might increase the risk of bleeding, although there is little clinical evidence supporting this link [47, 48]. Nevertheless, in the current study proposal we will exclude those subjects with a known bleeding disorder and those taking anticoagulants.

Subjects can, at any time, quit the study without any consequences for their standard clinical care. Disenrollment from the study might occur due to any of the following:Physician’s clinical assessmentSubject preferenceEmergent suicidalitySerious adverse eventsClinical evidence for need to increase or switch ongoing antidepressantWorsening clinical depression ratings by > 20%

### Blood sample analyzes

Hs-CRP as obtained before intervention start is analyzed according to standardized clinical procedure.

In addition to hs-CRP to determine inflammation/non-inflammation group status, 6 blood tubes are drawn at baseline, week 4 and week 8 (6 tubes each time point); two serum tubes and 4 ethylenediaminetetraacetic acid (EDTA)-tubes. The serum tubes are centrifuged (2000 g × 10 min, 20 °C) within 30–60 min after the blood is drawn. Serum is aliquoted (distributed) manually into 16 REMP-tubes (300 μL) with 200 μL serum in each tube. Two of the EDTA-tubes are frozen in a -80 °C freezer. The other 2 EDTA-tubes are centrifuged (2000 g × 10 min, 20 °C) and the plasma is aliquoted manually into 16 REMP-tubes (300 μL) with 200 μL serum in each REMP-tube. The blood samples are then transported (in a container on dry ice) to the biobank for storage. After all subjects have been recruited, we will analyze blood biomarkers of potential relevance to the study treatment such as inflammation, oxidative stress, metabolomics, endothelial function, and cell aging.

### Statistical considerations

Based on the primary outcome of a difference in HAM-D-17 score between baseline and eight weeks of treatment, the minimum difference of the primary outcome we want to demonstrate is 3. In order to reject the null hypothesis that the population mean is equal between the two groups with a power of 0.80 using a T-test, we estimated, in the original sample size calculation, that 45 patients with the outcome in each group are needed (alpha = 0.05).

This is, to the best of our knowledge, the first trial of its kind. The original sample size calculation was based on information from the most similar patient group we could find with regards to the variance of the primary outcome in the intervention groups. An external statistician, not involved in any other parts of the study, conducted an interim check of the standard deviation of the primary outcome measure, and the number of subjects in each group. This was done after approximately 2/3 of the total sample had been recruited. Based on the interim check, a new sample size calculation was performed, estimating that a total of 96 subjects are needed (power = 0.8, alpha = 0.05).

The statistical model to be used to analyze our outcome measures is *mixed model repeated measures*, with patient as a random effect and treatment group, treatment week (week four or eight) and the interaction of treatment group and treatment week as fixed effects.

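### As described, the primary mixed model assumes one common variance for weeks 4 and 8, so the week-8 test is miscalibrated in either direction if the two spreads differ; an unstructured covariance removes the dependence

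*Protocol article*

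**What the plan says.** Under Primary and secondary outcomes, the protocol article fixes the time point: "The primary outcome is absolute change in depressive symptoms between baseline and week 8", measured on the HAM-D-17.

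Under Statistical considerations it names a mixed model for repeated measures and gives its components: "with patient as a random effect and treatment group, treatment week (week four or eight", plus the group-by-week interaction. No residual covariance structure is stated, and no model contrast is named as the primary test.

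The same section sizes the trial on the week-8 change: "the minimum difference of the primary outcome we want to demonstrate is 3", "with a power of 0.80 using a T-test", giving "45 patients with the outcome in each group are needed (alpha = 0.05". An external statistician later "conducted an interim check of the standard deviation of the primary outcome measure", and the size was revised, "estimating that a total of 96 subjects are needed (power = 0.8, alpha = 0.05". Neither calculation reports the SD it used, and no SD is given for week 4 or week 8.

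**The concern.** The label and the description point to different models. A mixed model for repeated measures often means an unstructured covariance across visits, with a separate variance at each. A model whose only stated within-patient term is a random patient effect is, with ordinary software defaults, a random intercept with a single residual variance (compound symmetry).

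The difference matters because the primary comparison is at one visit. Under the random intercept, the standard error of the week-8 group difference uses the average of the week-4 and week-8 variances. If week-8 changes are more spread out than week-4 changes, that standard error is too small and the test rejects too often. If they are less spread out, it is too large and power is lost. The plan's own sizing used a t-test on the week-8 change, and hence the week-8 SD alone, so the literal model would not test the primary outcome with the variance the trial was sized on.

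**Working it through.** **Inputs from the protocol article.** Difference 3 points; power 0.80; alpha 0.05; t-test; 45 per group, later 96 in total; post-baseline visits at weeks 4 and 8.

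**Assumptions.** Two-sided alpha (sidedness is not stated); 96 split 48:48 (the split is not stated); a range for r = SD4/SD8, where SD4 and SD8 are the SDs of the analysed change at each visit.

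**Step 1: the plan's own figures.** Because no SD is given, 45 and 96 cannot be reproduced, only solved backwards. With two-sided noncentral-t power, 45 per group and a difference of 3 give 80% power at SD 5.02, and 48 per group at SD 5.19. I use SD8 = 5.2 for illustration. The error rates below depend on r and not on the level of SD8.

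**Step 2: what the literal model does.** With a random intercept and one residual variance, the variance at either visit is (patient variance + residual variance). With complete data at two visits this is estimated by the mean of the two visit variances. For the week-8 contrast:

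- model SE = sqrt{[(SD4² + SD8²)/2] × (1/n1 + 1/n2)}
- correct SE = sqrt{SD8² × (1/n1 + 1/n2)}
- SE ratio = sqrt[(r² + 1)/2]
- two-sided type I error = 2 × [1 − Φ(1.96 × SE ratio)]

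Example, r = 0.8: SD4 = 0.8 × 5.2 = 4.16. Mean variance = (17.31 + 27.04)/2 = 22.17. With 48 per group, model SE = sqrt(22.17 × 2/48) = 0.961 and correct SE = sqrt(27.04 × 2/48) = 1.061, so the ratio is 0.906. Type I error = 2 × [1 − Φ(1.775)] = 0.076.

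**Step 3: results over the assumed range.** The simulations used 40,000 complete-data trials per setting, 48 per group, within-patient correlation 0.5 and 0.7, and Satterthwaite degrees of freedom for the random intercept.

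| SD4/SD8 (assumed) | SE ratio | Type I error, formula | Simulated, common variance | Simulated, separate variances |
|---|---|---|---|---|
| 0.7 | 0.863 | 0.091 | 0.090–0.092 | 0.050 |
| 0.8 | 0.906 | 0.076 | 0.075–0.077 | 0.051 |
| 0.9 | 0.951 | 0.062 | 0.063 | 0.051–0.052 |
| 1.0 | 1.000 | 0.050 | 0.049–0.051 | 0.049–0.051 |
| 1.1 | 1.051 | 0.039 | 0.039–0.040 | 0.050 |
| 1.25 | 1.132 | 0.027 | 0.026–0.027 | 0.048–0.051 |

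The groups are formed by hs-CRP and need not be equal in size. With an assumed 32:64 split and r = 0.8, the simulated error was 0.074 with a common variance and 0.050 with separate variances.

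**Step 4: what is not affected.** The group-by-week interaction test held its level (0.048–0.051) at every ratio. Only the single-visit contrast is miscalibrated, and that contrast is the primary comparison.

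**The case against.** The strongest reply is that the article does not say the patient effect stands alone. A random patient effect can be combined with visit-specific residual variances. With two visits and positive covariance, that is equivalent to an unstructured matrix. The repeated-measures label itself often means unstructured. Covariance structure is also commonly left to a full protocol or analysis plan, neither of which is shown. This stands as far as it goes: the absence of a stated residual structure is not an error. The point concerns the component that is stated, which taken at its word gives a different model from the label.

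Three stronger readings are tempting and are not supported.

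- *The primary type I error is inflated.* A reader might infer this from the belief that change scores spread out over time. The documents give no visit-specific SD. Change is zero at baseline, so spread must grow at some stage, but that says nothing about weeks 4 to 8. Study procedures also lists worsening by more than 20% as a possible reason for leaving the study, which could trim later spread. The error may run either way or be nil.
- *The interaction p-value is the primary test.* It asks only whether the group gap differs between weeks 4 and 8, and a constant gap would leave it null. But nothing in the article gives it that role. The Abstract, the outcomes section and Statistical considerations all fix week 8, and the included interaction allows a week-8 contrast to be estimated.
- *Digit Symbol Coding shows that the model fails.* "The Digit Symbol Coding test is completed at baseline and week 8", so it has one post-baseline value. The week terms then drop out and the analysis reduces to a week-8 comparison. This is a minor matter of wording for one secondary outcome and does not bear on the primary test.

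**Conclusion.** The point holds conditionally. The described model, fitted literally, assumes equal variance at weeks 4 and 8, and the validity of the primary test then depends on that assumption. Moderate growth in spread (SD ratio 0.8 to 0.9) would understate the week-8 standard error by about 5% to 9% and put the type I error at about 6% to 8%; about 9% requires a ratio near 0.7. Shrinking spread makes the test conservative (about 4% at 1.1, 3% at 1.25), and equal SDs leave it at 5%.

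These figures rest on the literal reading of the model, assumed SD ratios, two-sided alpha and complete data; the effect of dropout has not been quantified. They do not show that the trial's p-value will be wrong. They show that its calibration depends on an assumption the plan need not make. The change is worth making before the analysis.

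**What to change.** In Statistical considerations, replace the random patient effect with an unstructured 2×2 within-patient covariance for weeks 4 and 8, fitted by REML with Kenward-Roger degrees of freedom. State that the primary test is the group contrast at week 8 from that model. With complete data its standard error is that of the week-8 t-test used for sizing.

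The cost is one extra variance parameter: three (two variances and a covariance) against two (patient and residual). If the variances prove equal, little is lost: with 48 per group and complete data, the week-8 contrast keeps 48 + 48 − 2 = 94 degrees of freedom. In the same edit, a clause can say that Digit Symbol Coding is compared at week 8 only.

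### The primary model omits baseline HAM-D-17, leaving the comparison of two non-randomised hs-CRP groups open to any difference in starting severity

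*Protocol article*

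**What the plan says.** Under Primary and secondary outcomes: "The primary outcome is absolute change in depressive symptoms between baseline and week 8", measured on the HAM-D-17.

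Under Study design: "This is a match-mismatch study with two parallel groups all receiving the same intervention". Group membership follows from pre-treatment hs-CRP (at least 3 mg/L, or below), so it is a patient characteristic and not a random allocation.

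Statistical considerations names a repeated-measures mixed model "with patient as a random effect" and, as its other terms, "treatment group, treatment week (week four or eight) and the interaction of treatment group and treatment week as fixed effects". The same section sets the planning difference: "the minimum difference of the primary outcome we want to demonstrate is 3". The sample size was derived "with a power of 0.80 using a T-test", first as 45 per group and then, after an interim check of the standard deviation, as 96 in total.

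No other section adds a baseline term or another way of handling a severity difference between the groups.

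**The concern.** Randomisation would make the groups' starting scores agree on average. Here nothing does, and the question is whether one group improves more than the other. Change on a rating scale usually depends on where the patient starts, so a group that begins higher can fall further without responding any differently to EPA.

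The model cannot separate these two explanations. Week has only the levels four and eight, so baseline is not one of the repeated measures. The patient random effect links a patient's two follow-up values, but it does not remove a difference between group means at baseline. What is at stake is whether a group difference in HAM-D-17 change can be read as differential response. Some precision may also be forgone, since the baseline score is already collected.

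**Working it through.** **1. The plan's own sample size.** No SD is printed, so I solved for it with difference 3, power 0.80, alpha 0.05 (two-sided assumed) and equal groups (assumed). The normal approximation is SD = 3 × √(n/2) / (1.960 + 0.842).
- n = 45 per group: 3 × 4.743 / 2.802 = 5.08 (5.02 with the exact t-test).
- n = 48 per group: 3 × 4.899 / 2.802 = 5.25 (5.19 with the exact t-test).

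Both figures are coherent with an SD of change just above 5. They cannot be independently reproduced, because the SD is not given. I use 5.19 to 5.2 and 48 per group below.

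**2. The shift.** Let b be the within-group slope of week-8 score on baseline, so the slope of change on baseline is b − 1. Let D be the baseline mean of the high hs-CRP group minus that of the low group. With complete data the model's week-8 contrast is the difference in mean change, and

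unadjusted contrast = baseline-adjusted contrast − (1 − b) × D.

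If both groups regress to a common mean, the adjusted contrast is the differential response and (1 − b) × D is spurious. Neither b nor D is in the document. Assumed values:

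| D (points) | b − 1 | Shift (points) | Share of 3 points | Chance of rejecting a true null |
|---|---|---|---|---|
| 1 | −0.3 | 0.3 | 10% | 5.9% |
| 1.5 | −0.4 | 0.6 | 20% | 8.7% |
| 2 | −0.5 | 1.0 | 33% | 15.4% |

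The last column is from the noncentral t. For 0.6 points, the standard error is 5.19 × √(2/48) = 1.06 and the noncentrality is 0.6 / 1.06 = 0.57. A simulation with b = 0.5 and D = 2 (48 per group, 4,000 runs) rejected in 15.3% of runs unadjusted and 5.2% with baseline in the model. These rates concern a systematic gap; chance imbalance alone is already covered by the test's standard error.

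**3. Precision.** With r the correlation of baseline with change, adjustment multiplies the residual variance by 1 − r².
- r = 0.3, 0.4, 0.5: factor 0.91, 0.84, 0.75, a reduction of 9% to 25%, worth 1/0.91 = 1.10 to 1/0.75 = 1.33 times the patients.
- These r values, paired with slopes of the same size, imply a baseline SD equal to the SD of change, about 5.2. The entry cut-off may narrow it. With an assumed baseline SD of 3 to 4, r = slope × baseline SD / 5.19 runs from 0.3 × 3 / 5.19 = 0.17 to 0.5 × 4 / 5.19 = 0.39, a reduction of 3% to 15%.
- Fixing instead the baseline-to-week-8 correlation at 0.3 to 0.5, with baseline SD 3 to 4 and SD of change 5.2, gives a factor of 0.75 to 1.00, a reduction of 0% to 25%.
- With equal SDs at baseline and week 8 the factor is (1 + ρ)/2, or 0.65 at ρ = 0.3, a reduction of 35%.

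**The case against.** The strongest objection is Lord's paradox. The groups are pre-existing. If each regresses to its own mean, the unadjusted change is the right contrast, and adding baseline introduces an error of the same size, (1 − b) × D. The 8.7% would then belong to the adjusted analysis. The document does not settle which assumption holds. This stands in full, and it is why both contrasts have to be shown.

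Several stronger readings are tempting but not supported.
- *The omission favours the trial's hypothesis.* The Background ties inflammation to a symptom profile (anhedonia, energy, sleep, appetite), and the Discussion notes HAM-D items on insomnia and weight loss. A higher start in the high hs-CRP group is therefore plausible. But no total-score difference is documented. If the low group starts higher, the shift works against the hypothesis; if the groups start level, it vanishes.
- *The HAM-D-17 entry threshold of 15 itself creates the problem.* It applies alike to both groups and is checked at screening. Scales are rated again at the baseline visit, so part of the regression it causes precedes the change score. Baseline measurement error remains.
- *The model ignores baseline altogether and compares week-8 levels.* The response is not stated beside the model, but the outcome definition makes change the natural reading, so baseline enters by subtraction. Only on raw scores would b × D carry over directly.
- *The sample size is wrong.* It was planned on an unadjusted t-test and does not rely on adjustment.

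Finally, this is a condensed article, and an analysis plan not shown could include the covariate. That carries limited weight, because the article names its fixed effects explicitly and baseline is not among them.

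**Conclusion.** The point holds in a conditional form and is a recommended change. What the text establishes is that the stated terms omit baseline HAM-D-17 in a comparison of non-randomised groups. What follows depends on assumptions: for D of 1 to 2 points, a change-on-baseline slope of −0.3 to −0.5 and regression to a common mean, the contrast shifts by 0.3 to 1.0 points, 10% to 33% of the target difference, in an unknown direction. It is not a demonstrated bias. The precision gain is secondary: it runs from near 0% to about 25% or more of the variance, and is likely at the lower end if the entry cut-off narrows the baseline spread.

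**What to change.** In Statistical considerations:
- State that the response is change in HAM-D-17 from baseline at weeks 4 and 8.
- Add baseline HAM-D-17 and baseline-by-week as covariates.
- Pre-specify the week-8 group contrast as primary.
- Pre-specify the unadjusted change contrast as a sensitivity analysis reported beside it, and treat a conclusion as robust only if the two agree.

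The cost is a few sentences and no new data, since the baseline score is already needed for the outcome. The downside is that with pre-existing groups the two estimates can legitimately differ, which leaves a less clear-cut conclusion. Adjusting for baseline severity also does not remove other confounders of hs-CRP, such as overweight and old age, which the Discussion itself names as influences on its level.
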